### Formative phase – Rwanda & Zambia

Country teams will interview participating ANC health workers and supervisors from the selected health facilities. Teams will conduct two FGDs with participating health workers (two per facility) from the health centres. These FGD will enable teams to understand user perceptions as well as enablers and barriers to implementing the country-adapted ANC digital module and its teaching and technical support mechanisms. An additional FGD or IDI will be held with the supervisors of the same health centres to gather their perceptions on the supervisory and mentoring tools developed for the country-adapted ANC digital module’s implementation in the demonstration phase.

### Demonstration phase – Rwanda & Zambia

At 5% significance, with 14 facilities we are powered (80%) to detect an approximate 20% difference in the proportion of women who complete their first contact in the first trimester with 100 women per facility per period (4 months). Baseline data in Table 1 present that on average, approximately 30% of women attend their first contact in the first trimester, and we assume an ICC of 0.1 and a CAC of 0.6 between both groups.

To account for possible data loss, we have increased the sample size by 20%. Therefore, we will recruit 120 observations per facility per period. This would yield a sample size of 1680 per period (840 per cluster, 30 per facility per month); for a total sample of 10 080 women attending their first ANC contact over the course of 24 months of data collection.

A summary table of the planned data collection processes, sample size and data sources are available in Table 5.

### Data analysis of quantitative data

A statistical analysis plan will be developed that describes in detail how the study data will be organized and analysed. In general, health facility and participant characteristics at baseline will be described according to the appropriate summary statistics, example proportions for categorical data, and mean, standard deviation, standard error and interquartile range for continuous data. Chi-squared test will be used to compare proportions for categorical variables and *t*-test will be used to compare means for continuous variables across facilities, clusters, and districts.

Impact on adherence to the adapted ANC package by health workers will be evaluated by comparing primary parameters (varies by country) at baseline prior to implementation to when the adapted ANC package is fully implemented. Hypothesis for comparing the proportions can be expressed formally as:$$H0: \, p1 = p2 \, vs \, H1: \, p1 \, < > \, p2$$where p1 and p2 are respective proportions at baseline and after ANC package implementation.

Hypothesis testing at *P* = 0.05 significant level will be conducted by regression analysis using generalized linear models (GLM) to estimate both the risk difference and relative risk. The GLM model for primary analysis will allow for adjustment for correlation due to clustering across time periods.

All descriptive and statistical analyses, including survey data, will be performed using Stata SE version 15.1.

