**Fig. 2 Fig2:**
[figure not shown]
**A**, **B** Stepped-wedge cluster implementation designs. *Pkg* package, *ANC* antenatal care. The blue outlines refer to the nested cohort recruitment and follow up periods

Health facilities will be randomly allocated to one of four clusters. The study period of 24 months will be divided into six periods of four months each. All selected facilities will cycle through the following steps:Baseline phase: Facilities will all begin with at least one four-month period of baseline data collectionPreparation phase: This will be a transition phase where all the co-interventions will be initiated.Full implementation phase: Depending on the cluster [1–4], health facilities will implement the ANC package for a range of either one to four periods (4–16 months). Please see Fig. 2A for more information.

Implementation of the adapted ANC package will be done cluster wise from period 2 onwards, such that by period 6 all clusters would have received the intervention. Data will be collected cross-sectionally at the end of each month in each cluster.

In addition to collecting cross-sectional data in each cluster every period, two cohorts of pregnant women will be enrolled and followed through the course of their pregnancy. One cohort will not be exposed to the intervention (comparison arm). For the comparison group, pregnant women in cluster 1 and cluster 2 will be enrolled during the first three months of period 1 and followed through to the end of their pregnancy (period 3). For the intervention group, pregnant women in clusters 3 and 4 will be enrolled. To ensure comparability, for cluster 3, women will be enrolled during the first three months of period 4 and followed through to the end of their pregnancy (period 6), while for cluster 4, women will be identified and consented during the first three months of period 3 and followed through to the end of their pregnancy (period 5). Purposive sampling will be used to identify women coming for their first ANC during the first trimester. Research teams will monitor selection to ensure a balance in maternal age, parity, education level and religion.

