#### For stepped-wedge cluster randomized trial (India)

For estimating the sample size for the stepped-wedge cluster randomized design, we utilized one of the primary indicators: proportion of pregnant women who were screened for syphilis during their pregnancy. The current estimates for this indicator are approximately 20% in both Tamil Nadu and Assam. Considering 20% as the baseline, and our study having 80% power to detect a minimum change of 15%, alpha error of 5%, cluster size of 100 per period, intracluster correlation coefficient (ICC) of 0.1 and cluster autocorrelation coefficient (CAC) of 0.8, the total sample size computed is 4800 women, or 800 per period. To account for issues around data loss (incomplete entries, errors in entries, etc.), we have further inflated this computed sample size by 20%. This results in a total sample of 5760 women, or 960 per period.

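### Baseline chi-squared and t-tests across clusters and districts ignore clustering by facility, so for a variable with ICC 0.1 and 120 women per facility they reject in up to about 58% (two clusters) or about 90% (four clusters) of comparisons under chance allocation alone

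*Protocol article*

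**What the plan says.** In *Data analysis of quantitative data*, a sentence on describing facility and participant characteristics at baseline is followed directly by the choice of tests. For categorical data: "Chi-squared test will be used to compare proportions for categorical variables". For continuous data, the sentence on the t-test continues: "test will be used to compare means for continuous variables across facilities, clusters, and districts". Neither is given an adjustment for correlation within facilities. The only such adjustment is tied to the main model: "The GLM model for primary analysis will allow for adjustment for correlation due to clustering across time periods".

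Elsewhere the article treats women in one facility as correlated and the facility as the unit allocated:

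- *Study design – India & Burkina Faso*: "Health facilities will be randomly allocated to one of four clusters".
- *Study design – Rwanda & Zambia*: facilities are matched in pairs and one of each pair is drawn at random to start first.
- *Demonstration phase – Rwanda & Zambia*: "we assume an ICC of 0.1 and a CAC of 0.6 between both groups". The India and Burkina Faso stepped-wedge calculations also use an ICC of 0.1.
- Both nested-cohort calculations apply a factor of 1.5 for grouping by facility.

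**The concern.** A chi-squared or t-test on individual women takes its null distribution from independent women. Here a cluster is a set of whole facilities, and women in one facility resemble each other. Two randomised clusters will therefore differ by more than independent sampling predicts, simply because of which facilities fell into each. An unadjusted test answers whether there is any facility-to-facility variation at all. The question for randomised clusters is whether they differ by more than chance allocation of facilities would produce.

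At stake is how the baseline tables are read. Correctly randomised clusters could routinely be marked as significantly different, and differences between districts could look better established than the number of facilities supports.

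**Working it through.** **Inputs.**
- Women per facility per period, m. Rwanda and Zambia: 100 × 1.2 = 120. Table 5 gives 120 for all countries. The Burkina Faso text gives 60 (60 × 4 × 4 × 2 = 1920 per period). Table 5 also has 1920 per period, but at 120 per facility that means 1920 / 120 = 16 facilities, not the 4 × 4 × 2 = 32 in the text. Both values of m are used below.
- ICC: 0.1, set for syphilis screening (India) and early first contact (the other countries). It is taken at facility level: India's 800 per period with 100 per unit means 8 units, not four. No ICC is given for background characteristics, so lower values below are assumptions.
- Groups compared: four clusters in India and Burkina Faso; two clusters of 7 facilities in Rwanda and Zambia.
- Level: two-sided 5%.

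**The plan's own figures.** The article states no error rate for these tests. The counts that supply m do reproduce: 14 × 120 = 1680 per period, and 1680 × 6 = 10 080.

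**Formulas.** Design effect DE = 1 + (m − 1) × ICC. With no true difference beyond chance allocation of facilities, the unadjusted statistic is inflated by about DE, so the rejection rate is P(χ²₁ > 3.84/DE) for two groups and P(χ²₃ > 7.81/DE) for four.

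For m = 120 and ICC 0.1: DE = 1 + 119 × 0.1 = 12.9. Two groups: P(χ²₁ > 0.298) = 58.5%. Four groups: P(χ²₃ > 0.605) = 89.5%.

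| m | ICC | DE | two clusters | four clusters |
|---|---|---|---|---|
| 120 | 0.1 | 12.9 | 58.5% | 89.5% |
| 100 | 0.1 | 10.9 | 55.3% | 86.9% |
| 60 | 0.1 | 6.9 | 45.6% | 76.9% |
| 120 | 0.05 (assumed) | 6.95 | 45.7% | 77.1% |
| 120 | 0.02 (assumed) | 3.38 | 28.6% | 51.0% |
| 120 | 0.01 (assumed) | 2.19 | 18.5% | 31.2% |
| 60 | 0.01 (assumed) | 1.59 | 12.0% | 17.8% |

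**Check by simulation.** Beta-binomial data with m = 120 and ICC 0.1 give 58.9% for two clusters of 7 facilities and 90% to 91% for four clusters. A t-test between two clusters on a normal outcome gives 58.6% to 59.4%.

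**Pair-matching (Rwanda and Zambia).** With an assumed within-pair correlation r of facility effects, DE falls to 12.9 − 120 × 0.1 × r. For r = 0.25, 0.5 and 0.75 this is 9.9, 6.9 and 3.9, and the rejection rate is 53%, 46% and 32%. So 58.5% is the unmatched upper value.

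**In plain units.** In Rwanda and Zambia, 840 women per cluster carry the information of 840 / 12.9 ≈ 65. At a proportion of 30%, the chance standard deviation of the difference is √(2 × 0.3 × 0.7 / 65) ≈ 8.0 percentage points before any gain from matching. The unadjusted test assumes √(2 × 0.3 × 0.7 / 840) ≈ 2.2 points.

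**The remedy.** In the same kind of simulation (ICC 0.01 to 0.1), one-way ANOVA on facility-level proportions rejected in 4.5% to 5.6% of runs.

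**The case against.** The strongest reply is that this is a brief, general sentence in an article that says "A statistical analysis plan will be developed that describes in detail how the study data will be organized and analysed", and that it concerns descriptive tables only. That limits the weight of the point but does not remove it. The tests are named, the groups they compare are named, and the adjustment is attached to a different analysis. A later plan that followed the text would carry the fault over.

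Several limits on scope stand in full:

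- The ICC of 0.1 belongs to outcome indicators. Age, parity or education may have a smaller one. A reader might infer that 58% to 90% of all baseline comparisons would be falsely significant; the article gives no ICC that supports this.
- Pair-matching lowers the rate in Rwanda and Zambia by an amount the article does not let us fix.
- *Target population* says that sub-national locations, districts included, were selected with the Ministries of Health, in some instances for high or low performance. Real differences between districts are to be expected, so chance-allocation rates do not describe those comparisons.
- Facility characteristics have the facility as unit and are unaffected. So are comparisons between named facilities, where the facility difference is itself the question.

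A reader might also infer that the baseline P values would be used to question the randomisation or to choose covariates, or that the effect estimates are compromised. Nothing in the article says the first two, and the third conflicts with the stated adjustment in the primary GLM.

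**Conclusion.** The point holds for comparisons of women's characteristics across randomised clusters. As written, the tests give P values that are too small. For a variable with ICC 0.1 and 120 women per facility, the rejection rate at nominal 5% is up to about 58% for two clusters and about 90% for four. It is about 77% for four clusters with the 60 women per facility of the Burkina Faso text, and about 19% and 31% at an assumed ICC of 0.01 with 120 women. These figures assume equal facility sizes, an ICC at facility level and, for two clusters, no gain from matching. The exact rate depends on an ICC that the article does not give, but every scenario computed lies well above 5%.

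District comparisons share the underlying flaw, in that variation between facilities within a district is ignored, but no rate can be attached to them from these calculations. The damage is confined to baseline P values; the primary analysis is not touched.

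**What to change.** In *Data analysis of quantitative data*, remove the woman-level chi-squared and t-tests across clusters and describe baseline characteristics by cluster instead, for example with the mean and range of facility proportions or means. Where a P value across clusters or districts is wanted, either test facility-level summaries or use a cluster-adjusted test. Facility-level summaries can be compared by ANOVA or, for clusters, by a permutation that respects the randomisation and, in Rwanda and Zambia, the pairs.

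The cost is about two sentences of wording and no extra data. The drawback is low power, because these comparisons would rest on few facilities: 14 in Rwanda and Zambia and 8 units in the India calculation. That reflects the information the design actually holds on such differences.

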### Study design – India & Burkina Faso

The study design is a mixed methods stepped-wedge cluster randomized design implementation trial with nested cohort study (in India and Burkina Faso) (Fig. 2A). The design involves a sequential crossover of clusters from the control to the intervention arm, so that every cluster, composed of selected primary health facilities, begins in the control condition and eventually receives the intervention, with random assignment to the order of crossover.

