The second, demonstration phase (24 months), employs a mixed methods stepped-wedge cluster randomized design implementation trial to test the introduction of the adapted ANC package and the digital tool in selected health facilities in both clusters (Fig. 2B). Facilities will be pair-matched on the basis of factors affecting ANC enrolment, quality and facility capacity. Within each pair, a facility will be randomly chosen to start implementing first the adapted ANC package, and then the adapted ANC digital module. All selected facilities will cycle through the following steps:Baseline phase: Facilities will all begin with at least one four-month period of baseline data collection. Cluster 1 facilities will collect an additional four months of baseline data.Preparation phase for the deployment of the national package of ANC interventions: This will be a transition phase where all co-interventions, except the digital module, will be initiated. Adapted ANC package implementation phase: Health facilities will then have four months to implement the adapted ANC package.Adapted ANC package implementation and preparation for deployment of country-adapted ANC digital module: This will be a transition phase where the digital co-intervention will be initiated; the other four co-interventions will continue to be implemented.Adapted ANC package and adapted ANC digital module implementation: Facilities will deploy both the adapted ANC package and the digital tool to assist health workers in implementing the former.

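### As written, the primary hypothesis compares baseline with post-implementation proportions and makes no adjustment for calendar period, which conflicts with the stepped-wedge design and with India's sample size

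*Protocol article*

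**What the plan says.** All of the analysis text is in the protocol article, under Data analysis of quantitative data. Impact on adherence is to be evaluated by "comparing primary parameters (varies by country) at baseline prior to implementation to when the adapted ANC package is fully implemented". The null hypothesis is p1 = p2, two-sided, "where p1 and p2 are respective proportions at baseline and after ANC package implementation". The test at the 5% "significant level will be conducted by regression analysis using generalized linear models (GLM) to estimate both the risk difference and relative risk". Time appears in one sentence only: "The GLM model for primary analysis will allow for adjustment for correlation due to clustering across time periods". The section opens by deferring detail: "A statistical analysis plan will be developed that describes in detail how the study data will be organized and analysed".

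The design text differs in kind. Under Study design – India & Burkina Faso, every cluster "begins in the control condition and eventually receives the intervention, with random assignment to the order of crossover". There are four groups of facilities and six periods of four months. Every facility has at least one baseline period, then a preparation phase, then one to four periods of full implementation. The India sample size paragraph uses both an ICC (0.1) and a cluster autocorrelation (CAC, 0.8).

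**The concern.** In a stepped wedge, exposure and calendar time are tied together: early facility-periods are all control and late ones are all intervention. Randomising the crossover order is useful because, in the middle periods, facilities that have crossed can be compared with facilities that have not. That comparison enters the estimate only if period is in the model for the mean. A baseline proportion set against a post-implementation proportion does not use it. Allowing for correlation across periods changes the covariance and hence the standard error; it leaves a trend in the mean where it was.

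At stake is attribution. If antenatal care changes over 24 months for reasons unrelated to the package, a test run as the text describes would credit that change to the package.

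**Working it through.** **Inputs from the article.** Six four-month periods; four crossover groups; full implementation for 4, 3, 2 or 1 periods. India: 20% baseline, +15 points, 100 per cluster-period, ICC 0.1, CAC 0.8, 80% power, two-sided 5%, 800 women per period, hence 800/100 = 8 facilities. Burkina Faso: 40% baseline, +10 points, ICC 0.1, 1600 per period over 4 × 4 × 2 = 32 facilities, hence 50 each; no CAC is stated.

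**Assumptions.** The preparation phase lasts one period and is excluded (the design figure is not shown). The background trend is linear. Its size is not in the documents; 2, 3 and 5 points per year are used.

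**Method.** Generalised least squares on facility-period means. The variance of a mean is p(1−p)[ICC + (1−ICC)/m]; the covariance between two periods of one facility is p(1−p)·ICC·CAC. For India at p = 0.20 and m = 100 these are 0.16 × (0.1 + 0.009) = 0.0174 and 0.16 × 0.08 = 0.0128. Power is Φ(effect/SE − 1.96). The rejection rate under no effect is Φ(bias/SE − 1.96) + Φ(−bias/SE − 1.96).

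**1. The plan's own figure (India, 4800 women).**

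| Model | Variance at | SE, 8 facilities | Power, 8 facilities (4800) | Power, 4 facilities (2400) |
|---|---|---|---|---|
| With period effects | 20% | 0.051 | 84% | 55% |
| With period effects | average, 27.5% | 0.057 | 75% | 46% |
| Without period effects | 20% | 0.024 | about 100% | 99% |
| Without period effects | average, 27.5% | 0.027 | about 100% | 98% |

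With period effects and baseline variance, 8 is the smallest multiple of four facilities that reaches 80%. The unadjusted test would already have 98% to 99% power at half the stated size. The match depends on the variant: if preparation is counted as intervention, 8 facilities give 96% to 98%, and 4 facilities give 73% at the average rate or 82% at baseline variance. No variant makes 4800 the size needed for the before/after test. For Burkina Faso, 1600 per period gives about 80% with period effects if CAC is 0.8.

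**2. How far apart in time the two conditions lie.** Baseline facility-periods by crossover group: 1; 1–2; 1–3; 1–4. Mean period = (1 + 3 + 6 + 10)/10 = 2.0. Full implementation: 3–6; 4–6; 5–6; 6. Mean period = (18 + 15 + 11 + 6)/10 = 5.0. The gap is 3 periods, or 12 months. With 8 facilities, the baseline/implementing counts by period are 8/0, 6/0, 4/2, 2/4, 0/6 and 0/8, so only periods 3 and 4 hold a concurrent comparison.

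**3. Bias without a period term, true effect zero.** A simple comparison of pooled means is biased by 1.0 times the annual trend (12 months). The weighted estimate that allows for correlation is biased by about 1.15 times. With fixed period effects the bias is 0.

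| Trend, points/year | Bias, points | India, 8 facilities, baseline variance | India, average rate |
|---|---|---|---|
| 2 | +2.3 | 16% | 14% |
| 3 | +3.5 | 31% | 25% |
| 5 | +5.8 | 68% | 58% |

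Example at 3 points: 0.0346/0.0239 = 1.448, and Φ(1.448 − 1.96) + Φ(−1.448 − 1.96) is about 0.305.

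Burkina Faso at 3 points per year and baseline variance: about 34% at CAC 0.5, 54% at CAC 0.8 and 85% at CAC 1.0.

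**4. Rwanda and Zambia.** There are two groups of seven facilities. One has one baseline period and the other has two. With one preparation period excluded, the baseline/implementing counts by period are 14/0, 7/0, 0/7, 0/14, 0/14 and 0/14. No period holds both conditions. A model with six period effects and one intervention effect has rank 6 for 7 parameters, so the period-adjusted effect cannot be estimated. If the preparation period is assigned to one condition, the effect can be estimated, with power of 89% to 93% for the stated 20-point difference.

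**The case against.** The strongest reply is that the article does not exclude period effects; it is silent on them, and it promises an analysis plan. Baseline and full implementation are also the names of design phases, so p1 = p2 could be shorthand for control versus intervention under staggered crossover. Using a CAC, and a sample size that fits a period-adjusted model, suggests that such a model was intended.

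Much of this stands. A reader might infer that the trial's final estimates will equal the true effect plus the trend, or that no significant result could be attributed to the package. The documents do not support that: the analysis plan is not shown and may add period effects. A reader might also infer that an upward trend is likely because antenatal care policy has been adapted since 2018. The article reports no change over time in any of the outcomes, so the trend remains an assumption. That the matched pairs used to randomise in Rwanda and Zambia, or a small-sample correction, go unmentioned is ordinary analysis-plan detail and no finding.

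The reply does not remove the core. The article goes beyond silence: it states a contrast and a null hypothesis, and its only time-related provision concerns correlation. An analysis plan that follows this text inherits the problem; one that adds period effects departs from the published hypothesis. If a period-adjusted analysis was intended, the sample size and the stated test disagree.

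**Conclusion.** The point holds for the hypothesis and primary model as the article states them. They contain no calendar-period adjustment, they do not use the comparison that the randomised order creates, and they do not match India's sample size. It is not a finding about the analysis eventually run.

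The bias is about 1.15 times whatever annual trend exists, given a one-period preparation phase that is excluded. The false-positive rates rest on assumed trends, on the variance chosen and, for Burkina Faso, on an unstated CAC; they show scale and are not forecasts. With no trend there is no bias. For Rwanda and Zambia a period term alone may not be enough, because under the same preparation assumption the two conditions never overlap in time.

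**What to change.** Restate H0 as a period-adjusted intervention effect of zero. Estimate the risk difference and relative risk in a model with a fixed effect for each four-month period, an intervention indicator, and facility and facility-by-period random effects, or an equivalent GEE. State whether preparation periods are excluded or assigned to a condition.

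For Rwanda and Zambia, either assign the preparation period to a condition, or use monthly calendar time with a stated definition of when exposure begins. Monthly time alone does not help if four full preparation months are excluded: the earlier group would start implementing in month 9, and the later group's baseline ends in month 8. If neither is adopted, say plainly that the estimate there is a before/after comparison.

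For India and Burkina Faso this is a change of wording in the protocol and analysis plan. The cost is precision. India's standard error roughly doubles (0.051 against 0.024 at baseline variance, 0.057 against 0.027 at the average rate), and period-adjusted power is about 75% to 84% depending on the variance used, so it may fall below the planned 80%. Burkina Faso should state its CAC, since its adjusted power depends on it.
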